### Other sources of information and covariables

Participants’ anthropometric, sociodemographic and reproductive features will be recorded. They will also grant permission to access their clinical history.

#### Anthropometric and sociodemographic information

Age, race, weight, height, residence area (rural/urban), marital status, education, current working activity, social class, smoking habits (never, current, former), and alcohol consumption (never, current, past), will be recorded.

#### Reproductive history

Age of menarche and menopause status (premenopause, postmenopause), number of pregnancies, number of sons, age at the first and last pregnancy, total duration of breast feeding, use of hormonal contraceptives and/or substitute hormonal therapy (age at beginning and duration).

#### Tumor features

Type and hystological grade according to the International Classification of Oncological Diseases (CIE-0-2); tumor stage: clinical and anatomopathogical TNM (malignant tumor classification); hormone receptors (estrogens and progesterone); HER2, and tumor markers (pS2, cathepsin D and p53).

#### Diet

Participants will answer two questionnaires: adherence to the Mediterranean diet and frequency of food consumption.

### Statistical analysis

Relative abundance of the microbes will be expressed as median ± range. Differences among microbes will be calculated by the *U*-Mann de Whitney. Intestinal and mammary microbiota clusters will be calculated by an analysis of principal components made with the bioinformatic data. Those data will be normalized between 0 and 1, and the Euclidean distance will be evaluated. A permutation ANOVA (PERMANOVA) will be carried out with the PRIMER 7 software. Finally, a tree diagram will be built for each evaluated group based on the different taxonomic scales.

For metabolomic statistical analysis and data display purposes, any missing values will be assumed to be below the limits of detection, and these values will be imputed with the compound minimum (minimum value imputation). The data will be tested for variance homogeneity, and if there were unequal variances, the data will be log-transformed. The statistical analysis of the data will be performed using Array Studio (OmicSoft, NC, USA) and proprietary software from Metabolon. A t-test for equality of the means will be carried out between the intestinal and mammary microbiota and for each metabolite to determine differences. A *p*-value 0.05 will be considered statistically significant. A one-way ANOVA, assuming homogeneity of variance, will be used to determine whether at least two unknown means are all equal or at least one pair of means is different. In case that the variances were unequal, a Welch-ANOVA will be performed. The false discovery rate (q-value) will be calculated to take into account the multiple comparisons that normally occur in metabolomics-based studies, thus estimating the reliability of the results. A q-value 0.1 will be considered statistically significant.

Random forest (RF) is a supervised classification technique based on an ensemble of decision trees [35] with several advantages. It makes no parametric assumptions, and variable selection is not needed. It does not overfit, and it is invariant to transformation. In RF analysis, it is not necessary to cross-validate or do a separate test set to obtain an unbiased estimate of the test set error. A “variable importance” measure will be computed to determine which variables (metabolites) make the largest contribution to the classification. The mean decrease in accuracy (MDA) will be used as this metric and will be determined by randomly permuting a variable, running the observed values through the trees, and then reassessing the prediction accuracy. If a variable were not significant, then this procedure will have little change in the accuracy of the class prediction (permuting random noise will give random noise). By contrast, if a variable is relevant for the classification, the prediction accuracy will drop after such a permutation, which will be recorded as the MDA. Thus, the RF analysis provides an “importance” rank ordering for biochemicals [35].

Participants will be grouped into tertiles of urinary EDC levels based on their distributions among the controls. Odds ratios and 95% confidence intervals (CIs) for breast cancer comparing the second and third tertiles with the first tertile will be estimated using logistic regression models. Further, associations of participant characteristics with urinary EDC levels, estrogens and estrogen metabolites and fecal microbiome measures will be evaluated by using general linear models and testing either for differences across categories or for trends across categories. Linear regression models will also be used to evaluate associations of each steroid measure with measures of the diversity of the fecal microbiome, abundance and with taxonomic groups at phylum and family levels, adjusting by covariates.

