The hypothesis of this study is that the risk of breast cancer could be associated with the composition and functionality of the mammary and/or intestinal microbiota. The hypothesis is supported by preliminary studies which suggest that the microbial pattern of women with breast cancer is different than that of healthy women, not only with regards to bacterial types and relative abundance, but also with their functionality (metabolic capacity, ability y to damage DNA, etc.) [27, 37–39]. Exogenous factors such as the exposure to EDCs might contribute to this altered pattern [40, 41]. These circumstances would attribute to the microbiota the possibility of acting as an additional environmental risk factor and a potential prognostic modulator of the disease.

Validation of the hypothesis could translate into new recommendations and guidelines of clinical practice to improve prevention and prognosis of breast cancer, alleviating the burden of this disease. Likewise, a better identification of those patients most likely to efficiently respond to treatment could derive, given the fact that efficacy of immunotherapy against cancer depends on patients’ intestinal microbiota [42, 43]. Finally, interventional clinical studies aimed at shifting the mammary/gut dysbiosis of women affected by breast cancer toward a composition similar to that of healthy women could be designed.

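### The hypothesis is about microbiota and breast cancer risk, but the only stated association measure for breast cancer is an odds ratio for urinary EDC tertiles

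*Protocol article*

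**What the plan says.** The Discussion gives the hypothesis as: "the risk of breast cancer could be associated with the composition and functionality of the mammary and/or intestinal microbiota". The Abstract says much the same, and the Discussion states the aim as a connection with the risk of developing the disease.

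The Statistical analysis section treats the exposures differently.

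- **Microbiota, description:** "Relative abundance of the microbes will be expressed as median ± range".
- **Microbiota, single taxa:** "Differences among microbes will be calculated by the" Mann-Whitney U test. The groups compared are not named.
- **Microbiota, whole community:** principal components, then "Those data will be normalized between 0 and 1, and the Euclidean distance will be evaluated", then "A permutation ANOVA (PERMANOVA) will be carried out with the PRIMER 7 software". The grouping factor is not named. Tree diagrams follow for each evaluated group.
- **Urinary EDCs:** "Participants will be grouped into tertiles of urinary EDC levels based on their distributions among the controls", followed by "Odds ratios and 95% confidence intervals (CIs) for breast cancer comparing the second and third tertiles with the first tertile", from logistic regression.
- **Fecal microbiome in regression models:** general linear models against participant characteristics, and linear models for "associations of each steroid measure with measures of the diversity of the fecal microbiome, abundance and with taxonomic groups" at phylum and family levels, adjusted for covariates.

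Controls are matched to cases on age (± 2 years), BMI category and hospital (Inclusion and exclusion criteria). At least 100 cases and 100 controls are planned (Sample size).

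**The concern.** A hypothesis about risk calls for an estimate of how strongly the exposure goes with being a case, and how precisely. The article states one for EDCs but not for the microbiota. Followed as written, the study could report that a taxon differs between groups without saying by how much the odds of being a case change. A non-significant result could not be separated from an imprecise one.

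Adjustment is also at stake. The Discussion names diet, smoking, age and alcohol among the factors that affect the microbiota, and says questionnaires are used to try to control some of them. A Mann-Whitney test can use neither those data nor the matching. The article attaches covariate adjustment only to the linear models with steroid measures, and those cover fecal microbiota only. Breast tissue microbiota appears in no regression model.

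The descriptive summary is a smaller matter. A range is not a ± quantity around a median, depends on the two most extreme women and tends to widen as the group grows.

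**Working it through.** **1. Which analysis gives what, as stated**

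| Analysis | Exposure or measure | Set against case status? | Size of association with CI? | Matching or covariates stated? |
|---|---|---|---|---|
| Median ± range | taxon abundance | not stated | no | no |
| Mann-Whitney | taxon abundance | groups not named | no | no |
| Principal components, PERMANOVA | community distance | factor not named | no | no |
| Tree diagrams | taxonomy by group | groups not named | no | no |
| General linear models | fecal microbiome measures | no, participant characteristics | coefficients, not for case status | not clearly |
| Linear models | fecal diversity, abundance, phylum and family | no, steroid measures | coefficients, not for case status | covariates |
| Logistic regression | urinary EDC tertiles | yes | odds ratio, 95% CI | none named |

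Only the last row gives a size of association with breast cancer, and its exposure is not the microbiota. Diversity is named in the analysis only in the steroid models.

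**2. Is an odds ratio for microbiota feasible at the planned size?**

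The article gives no numerical inputs for its sample size, so 100 + 100 cannot be reproduced. I take it as given, and the point does not depend on it. The calculations below assume unmatched analysis, two-sided 5% and no multiplicity adjustment.

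*Per SD of a continuous measure, near the null.* SE(log OR) ≈ 1/√(N × 0.5 × 0.5) = 1/√(200 × 0.25) = 0.1414.

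- 95% limits: exp(1.96 × 0.1414) = 1.32, so ×/÷ 1.32. An estimate of 1.0 would carry limits of 1/1.32 = 0.76 to 1.32.
- Odds ratio per SD with 80% power: exp((1.960 + 0.842) × 0.1414) = exp(0.396) = 1.49.

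*Standardised difference detectable with 80% power.* For a t-test: (1.960 + 0.842) × √(2/100) = 0.40. For Mann-Whitney under normality: (1.960 + 0.842) × √(2/(100 × 0.955)) = 0.41. On the log scale, the odds ratio of 1.49 is 0.396. Reporting an estimate therefore costs essentially no power against the stated test.

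*Tertile odds ratio near the null, about 33.3 women per cell.* SE = √(4/33.3) = 0.347 and exp(1.96 × 0.347) = 1.97. Per-SD modelling is clearly the more precise.

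*Carriage of a taxon, assumed present in one third of controls.* The case proportion is p1 = OR × p0 / (1 − p0 + OR × p0).

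| Odds ratio | p1 | Power, 100 v 100 |
|---|---|---|
| 1.5 | 0.429 | 0.28 |
| 2.0 | 0.500 | 0.67 |
| 2.25 | 0.529 | 0.80 |
| 3.0 | 0.600 | 0.97 |

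At an odds ratio of 1.5, most studies of this size would find nothing significant. There an interval says far more than a p-value.

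**3. Range as a measure of spread**

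For a normal variable the expected range is about 4.5 SD at n = 50, 5.0 SD at n = 100 and 5.5 SD at n = 200. The interquartile range is about 1.35 SD at any n. The range thus changes with group size when the population does not.

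**The case against.** The strongest reply is that this is a condensed article without its analysis plan. The effect measure that accompanies a Mann-Whitney test, or whether a diversity index is tabulated by group, may well be set out elsewhere. That stands for anything merely unmentioned. It does not remove the mismatch, because the article does assign methods by exposure and gives the association measure to EDCs.

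Several stronger readings are tempting, but the article does not support them.

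- *Diversity is never compared between cases and controls.* PERMANOVA on distances compares between-sample diversity, and its unnamed factor may be case status. Only the narrower statement holds: no case-control comparison of a within-sample index is stated.
- *Microbiota gets p-values only.* The linear models yield coefficients, though not against case status as written.
- *The steroid models miss the point.* The Background says gut diversity and composition may act through estrogen levels and inflammation. Those models address the estrogen part.
- *The article concludes that microbiota is a risk factor.* The Discussion speaks only of a possibility, and the Background aims at correlation. Group comparison is a legitimate first step towards that.
- *The spread of abundances can be put as a fold-range.* That needs a log-SD, which the article does not give.

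Two objections shape the remedy. The q-value in the article is tied to metabolomics, so it is not a stated gate for taxa. Odds ratios shown only for taxa that pass a significance screen in the same women would be inflated by selection and would leave null taxa without intervals. In addition, the interquartile range is 0 to 0 when more than three quarters of women lack a taxon, so it needs the share of carriers beside it.

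**Conclusion.** The point holds in its narrow form. The hypothesis links microbiota to breast cancer risk, yet the stated microbiota methods give no matched or covariate-adjusted size of association with case status. The one odds ratio with a confidence interval belongs to urinary EDCs. No bias in any planned result has been shown. The loss is in what the results can say, and the change is worth making but not critical.

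An odds ratio per SD with limits of about ×/÷ 1.32 is within reach at 100 v 100. That figure assumes no matching, no adjustment, values near the null and complete data, so real intervals will be somewhat wider. A reader might infer that such an odds ratio would show how microbiota raises risk. It would not: cases are enrolled on the day of diagnosis, stool is collected the day before surgery and tissue is taken during surgery. The estimate describes association only.

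**What to change.** For stool and for breast tissue separately:

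- Fit a logistic model for case status with a within-sample diversity index (for example Shannon at a common sequencing depth), per SD.
- Fit the same model for each taxon in a set fixed in advance, for example phyla and families above a stated prevalence cut-off. Trial status says data analysis is already under way, so choose the set without reference to case-control results already seen.
- Respect the matching on age, BMI category and hospital, by conditional logistic regression if matching is individual or by including these factors if it is not. Adjust for a named list of the collected covariates.
- Report odds ratios with 95% CIs for every measure tested, significant or not, with false-discovery control across taxa.
- Name the groups compared by Mann-Whitney and the PERMANOVA factor.
- Replace median ± range by median with interquartile range plus the share of women carrying the taxon.

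The cost is analysis wording and more models on data already being collected, with no new samples. Intervals will be somewhat wider than ×/÷ 1.32 after matching and adjustment, and the report should say that the odds ratios come from samples taken after diagnosis.

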## Discussion

There are 7 studies registered in ClinicalTrials.gov dealing with breast cancer and microbiota, 2 already completed and 4 currently ongoing. Of the 2 completed studies, one investigated the antibiotic profilaxis in oncological surgery of the breast, and the other investigated the relationship between intestinal bacteria and breast cancer risk. As for the studies in progress, these are trials investigating various intervention strategies (probiotics, physical activity, diet), the effects of gut microbiome on the neoadjuvant chemotherapy-induced immunosurveillance in triple negative breast cancer, or the effects of chemotherapy on gut bacteria in newly diagnosed breast cancer. Our study is a case-control clinical trial that aims at ascertaining the connection relating i) the composition of both gut and breast microbiota, ii) the functionality of both gut and breast microbiota, and iii) the exposure to environmental contaminants with the risk of developing breast cancer. To the best of our knowledge, it is the first study undertaking the simultaneous analysis of the microbiota of the mammary tissue and the intestine, and also the first attempt to link the microbiome with the EDC load and the risk of this disease.

The microbiota is affected by either modifiable and unmodifiable factors such as genetics, stress, diet, physical activity, lactation, delivery mode, antibiotic treatment, smoking, age, and alcohol consumption, among others [36]. For this reason, in an attempt to control some of the modifiable factors, all participants will answer three questionnaires to record their sociodemographic data, adherence to the Mediterranean diet, and frequency of food consumption. For the same reason, we set stringent inclusion and exclusion criteria. Women participating in the study will be newly diagnosed cases of breast cancer. Therefore, women with antecedents of cancer or advanced tumor stage will not take part, nor those who have received antibiotic treatment 3 months prior to recruitment, or any neoadjuvant therapy. Likewise, regarding the controls, women with oncological, gynecological or endocrine antecedents and those who have received antibiotic treatment 3 months prior to recruitment will not be included.

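### The test fixed for microbe differences cannot use the lifestyle and reproductive covariates that the protocol collects, so differences between cancer cases and breast-surgery controls could appear as cancer-associated taxa

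*Protocol article*

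**What the plan says.** All references are to the protocol article.

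- **Why these factors matter.** The Discussion lists influences on the microbiota: "genetics, stress, diet, physical activity, lactation, delivery mode, antibiotic treatment, smoking, age, and alcohol consumption, among others". It then gives the response: "in an attempt to control some of the modifiable factors, all participants will answer three questionnaires". Two of the three questionnaires concern diet and the third is sociodemographic. The exclusion criteria are presented as part of the same effort.
- **What is collected.** The section Other sources of information and covariables covers smoking and alcohol (three categories each), diet ("Participants will answer two questionnaires: adherence to the Mediterranean diet and frequency of food consumption") and, under Reproductive history, numbers of pregnancies and children and "total duration of breast feeding".
- **Design.** Controls are women having breast augmentation or reduction, matched on age (± 2 years), BMI category and hospital (Inclusion and exclusion criteria). At least 100 cases and 100 controls are planned (Sample size).
- **Microbiota analysis.** Statistical analysis states: "Differences among microbes will be calculated by the *U*-Mann de Whitney". It adds: "A permutation ANOVA (PERMANOVA) will be carried out with the PRIMER 7 software". No factor, covariate or stratum is named for either.
- **Where adjustment is stated.** Covariate adjustment is mentioned once, in the sentence that begins: "Linear regression models will also be used to evaluate associations of each steroid measure with measures of the diversity of the fecal microbiome". General linear models also relate participant characteristics to EDCs, estrogens and fecal microbiome measures.

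**The concern.** Recording a factor does not control it. Control needs restriction, matching or adjustment, and for diet, smoking, alcohol, parity and breast-feeding the article states none of these in the comparison that tests its central hypothesis.

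Women who have cosmetic or reduction surgery are a selected group and may differ from women with breast cancer in habits and reproductive history. A taxon that merely follows such a habit would then differ between the groups and be read as related to cancer. The Discussion expects the results to inform prevention guidance and trials that aim to shift the microbiota, so a false lead could travel far. The data needed to guard against this are already being gathered.

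**Working it through.** **1. Tracing each factor through the plan**

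| Factor | Recorded | Matched | In the Mann-Whitney test | Named for the PERMANOVA |
|---|---|---|---|---|
| Age, BMI category, hospital | yes | yes | no | no |
| Diet | yes | no | no | no |
| Smoking, alcohol | yes | no | no | no |
| Parity, breast-feeding | yes | no | no | no |

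The other models do not fill the gap. The logistic models concern tertiles of urinary EDCs. The steroid regressions have no stated case-control term. The general linear models describe how characteristics relate to the fecal microbiome. Neither of the last two covers the breast-tissue microbiota.

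**2. Size of the possible bias**

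The article gives no figure to reproduce here: no lifestyle difference between groups and no covariate-taxon correlation. Inputs:
- n = 100 per group (Sample size).
- Two-sided 0.05. The article states 0.05 for metabolomic tests and gives no level for microbiota tests, so this is assumed.
- A covariate differing by d = 0.3, 0.5 or 0.8 SD between groups, correlated r = 0.2, 0.3 or 0.4 with log abundance within groups (assumed).
- No true relation of the taxon to cancer.

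The spurious group shift is r × d in SD units. The Mann-Whitney test statistic is then centred near

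δ = r × d × √(n/2) × √(3/π) = r × d × 7.07 × 0.977,

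and the rejection rate is P(Z > 1.96 − δ) + P(Z < −1.96 − δ).

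For d = 0.3, r = 0.2: δ = 0.06 × 6.91 = 0.41, giving 7.0%. For d = 0.8, r = 0.4: δ = 0.32 × 6.91 = 2.21, giving 59.9%.

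Simulated rates (4,000 runs per cell), with the formula in brackets:

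| d | r = 0.2 | r = 0.3 | r = 0.4 |
|---|---|---|---|
| 0.3 | 6.8% (7.0) | 9.9% (9.5) | 13.2% (13.2) |
| 0.5 | 10.0% (10.6) | 17.4% (17.9) | 27.9% (28.2) |
| 0.8 | 20.6% (19.8) | 38.5% (38.2) | 58.5% (59.9) |

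With d = 0 the rate stays at about 5%. A rank regression on case status and the covariate gave 4.6% to 5.6% in every cell.

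**3. Same question with a binary factor**

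The factor shifts log abundance by 0.5 to 1.0 SD (assumed):

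| Prevalence, cases v controls | Mann-Whitney | Adjusted |
|---|---|---|
| 40% v 40% | 4.7–5.0% | 4.7–5.1% |
| 40% v 30% | 5.9–9.4% | 4.6–5.4% |
| 50% v 30% | 9.9–23.9% | 5.1–5.6% |
| 60% v 30% | 16.8–47.1% | 5.0–5.8% |

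**4. Covariate measured with error**

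Diet comes from questionnaires. If reliability is λ, a shift of about r × d × (1 − λ) remains after adjustment. Over the grid in step 2, the adjusted false-positive rate was about 5–10% at λ = 0.7 and about 6–20% at λ = 0.5 (both assumed). That is better than no adjustment but not nominal.

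**5. Price of adjusting**

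- With no imbalance, power for a 0.4 SD effect is Φ(0.4 × 7.07/√(1 − r²) − 1.96): 81% at r = 0, 84% at r = 0.3, 90% at r = 0.5. This is a small gain.
- With imbalance d, the standard error grows by √(1 + d²/4): 1% at 0.3, 3% at 0.5 and 8% at 0.8, partly offset by the factor √(1 − r²).

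**The case against.** The strongest reply is that this is condensation. The article heads the section that collects these items as covariables, mentions covariate adjustment without listing any covariates, and lists none for its logistic models either. A full protocol or analysis plan could hold the lists. This stands as far as the PERMANOVA goes: that method can take covariates, and the article does not say whether it will. A reader might infer a commitment to an unadjusted PERMANOVA by group, but the text names no factors at all. The reply does not rescue the univariate test, because the article names a specific procedure that no covariate list can be added to.

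Three further points stand:
- The article does not spell out that the Mann-Whitney test compares cases with controls. The study aim makes that the natural reading.
- A reader might infer that breast-feeding duration is recorded because it alters the microbiota. Lactation is on the Discussion's list, but the item sits under Reproductive history with no stated purpose, and the Discussion claims only an attempt at controlling some modifiable factors.
- The size rests wholly on assumed inputs. The top of the range needs a 0.8 SD imbalance together with a correlation of 0.4, and nothing in the article supports or excludes that.

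**Conclusion.** The point holds in a limited form. The article promises an attempt at control, collects the covariates, and fixes for microbe differences a test that can use none of them. Matching and the one stated adjustment do not cover the gap.

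The resulting bias is possible, not shown. Under imbalances of 0.3 to 0.8 SD and correlations of 0.2 to 0.4, the false-positive rate per taxon is about 7% to 59% instead of 5%. Without imbalance there is no inflation. The direction does not depend on the exact inputs: any imbalance in one factor that is related to abundance raises the error of the unadjusted test.

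Two stronger conclusions are not supported: that the study's microbiota results will be confounded, since the article gives no data on how the groups differ, and that adjustment would remove all confounding, since questionnaire error leaves some behind. The change is worth making because it is cheap, uses data already collected and, with enrolment and analysis under way, is best fixed before results shape the choice.

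**What to change.** In Statistical analysis, for each taxon and diversity measure, in stool and in breast tissue:

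1. Base conclusions about association with cancer on a regression of the rank-transformed measure on case status. Adjust for the matching factors (age, BMI category, hospital) and for Mediterranean diet score, smoking, alcohol, parity and total breast-feeding duration. Fixing the rank transformation avoids a later choice and the problem of taking logs of zero abundances.
2. In the PERMANOVA, name the factors and enter the same covariates before case status.
3. Keep the Mann-Whitney U as an unadjusted description.
4. Report adjusted and unadjusted results side by side. Cases are enrolled on the day of diagnosis and give stool the day before surgery (Biological samples), so diet may have changed in between.

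Cost: a change of wording and some extra analysis, with no new data. With diet score, parity and breast-feeding entered as linear terms, the covariates use 10 degrees of freedom (age 1, hospital 2, diet 1, smoking 2, alcohol 2, parity 1, breast-feeding 1), plus the number of BMI categories minus one, out of 200 women. Intervals widen somewhat where a covariate differs strongly between groups, a few women are lost to incomplete questionnaires, and some confounding remains through questionnaire error.
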